**E. Vitamin D, cardiovascular disease and the immune system**

It is probable that vitamin D has important immunomodulatory effects. Identification of vitamin D receptors (VDRs) in peripheral blood mononuclear cells sparked an early interest in vitamin D as an immune regulator.(63-65) Helper T (Th) cells are central to all antigen-specific immune responses. Th-1 cells secrete multiple pro-inflammatory cytokines including tumor necrosis factor (TNF), which are essential for cell-mediated immune responses. Th-2 cells play an important role in antibody-mediated immunity. The balance of Th cell responses dictates the outcome of any given challenge to the immune system. Both Th-1 and Th-2 cells are known targets of 1-25(OH)2D3. Vitamin D causes a relative shift away from Th-1 profile and toward a Th-2 like profile.(66) The end result of these changes is a switch away from a pro-inflammatory cytokine profile to a more anti-inflammatory profile.(67-70) Given this, it is not surprising that vitamin D deficiency has been associated with an increased risk of Th-1 cytokine-mediated autoimmune diseases such as inflammatory bowel disease, rheumatoid arthritis, systemic lupus erythematosis, multiple sclerosis, and type 1 diabetes mellitus.(71-73)

Inflammation is thought to be a major process mediating accelerated progression of atherosclerosis and its complications.(74) Manifold pathways tightly link inflammation with early development of atherosclerosis and plaque rupture.(75-77) Various inflammatory factors including interleukin 6 (IL-6), TNF, and CRP are considered to be actively involved in atherogenesis and contribute to plaque instability, thrombosis and acute coronary syndromes.(78-80) Activation of endothelial cells leads to expression of various cell adhesion molecules (CAMs) that are responsible for mediating cell-cell interaction between immune system and the endothelium. Upregulation of CAMs is a dynamic process sensitive to inflammatory cytokines. Levels of certain CAMs (ICAM-1 and VCAM-1) are thought to be indicators of inflammation and early atherosclerosis.(81-83) CRP has been shown to predict CV risk, independent of traditional predictive factors.(84-86) IL-6 levels are increased both in stable CAD and acute coronary syndromes,(75) and cardiomyopathies.(87) Several studies evaluated the predictive CVD value of IL-6 in healthy individuals independent of other inflammatory markers.(88) This may also be true in those with established CAD.(89) TNF- also seems to have predictive value for CV outcome in adults with (90) and without underlying CVD.(91) In the ABC study,(87) a composite summary indicator of inflammation, including CRP, TNF- and IL-6, showed a strong association with incident CVD and congestive heart failure in patients without CVD. Those with elevation of all three indicators in the highest tertile had a 2-3 fold higher risk.

Vitamin D treatment has been shown to inhibit production of ICAM-1,(92-94) VCAM-1 (93, 95) and cytokine production (56, 70, 96) both *in vitro* and *in vivo* settings. In summary, it is plausible that vitamin D deficiency leads to increases in pro-inflammatory cytokines, thereby contributing to the development and progression of CVD. This initial pilot work will begin to explore this possibility by evaluating the effect of vitamin D status on both endothelial function, arterial stiffness and plasma biomarkers of inflammation in postmenopausal women prior to, and following four months of treatment with vitamin D.

**HYPOTHESES AND SPECIFIC AIMS**

Our fundamental hypothesis is that low vitamin D status is a risk factor for CVD by causing a proinflammatory milieu, thereby leading to endothelial dysfunction. Additionally, we hypothesize that vitamin D supplementation will reduce inflammation, thereby restoring endothelial function and ultimately reducing CVD risk. To begin testing these hypotheses, the specific aims of this pilot study are to investigate:

1. The effect of vitamin D status, as defined by serum 25-hydroxyvitamin D [25(OH)D], on endothelial function, arterial stiffness, and selected plasma biomarkers of inflammation.
2. The effect of subsequent vitamin D therapy on endothelial function, arterial stiffness, and selected plasma biomarkers of inflammation.

To this end, we hypothesize that low vitamin D status is associated with increased circulating levels of inflammatory biomarkers. Though the primary outcome measure of this pilot study is change in markers of endothelial function and arterial stiffness with vitamin D3 therapy, changes in circulating inflammatory biomarkers are being proposed here as secondary outcome variables. If these hypotheses are correct, our long-term goals include investigation of the effect of vitamin D repletion on subclinical atherosclerosis and subsequent cardiovascular events. Ultimately, these future studies will be necessary to determine whether vitamin D supplementation could reduce future CVD events and mortality.

**STUDY DESIGN AND METHODS**

**Specific Aim #1. To investigate the effect of vitamin D status, as defined by serum 25-hydroxyvitamin D measurement, on endothelial function, arterial stiffness and plasma biomarkers of inflammation.** This study will utilize total of 80 postmenopausal women. At the screening visit, following informed consent, a baseline evaluation consisting of basic demographic information, including age, ethnicity, height, and weight will be collected. Clinical information will include personal and family medical history as well as medication and supplement use. Screening laboratory studies consisting of serum chemistry panel, 25(OH)D, and 24-hour urine calcium will be obtained. Subsequently, qualifying volunteers will return for a baseline visit at which time a complete physical examination will be performed, including blood pressure and pulse measurements. Laboratory data will be obtained, which will include fasting glucose, fasting lipid profile, plasma inflammatory biomarkers (i.e. hsCRP, IL-6, TNF-, ICAM-1 and VCAM-1), serum calcium, bone turnover markers and parathyroid hormone. The potential impact of vitamin D on endothelial function and arterial stiffness, which are surrogate markers for CVD, will be explored using noninvasive ultrasound technology and tonometry at baseline and again after four months.

**Specific Aim #2. To investigate the effect of vitamin D supplementation on endothelial function, arterial stiffness and plasma biomarkers of inflammation.** At the time of their baseline study visit, volunteers will be randomly assigned to receive either 2,500 IU D3 daily or placebo. Both volunteers and study staff will be blinded to the group assignment. Subsequent study visits will occur after one, two, and four months. Participants will return to the Osteoporosis Research Center in a fasting state for blood draw, which will be done between 0700 and 1100. Serum 25(OH)D and serum calcium will be measured at all of the time points. Fasting plasma glucose, fasting lipid profile, plasma biomarkers of inflammation, bone turnover markers and PTH along with brachial artery FMD and tonometry measurements will be repeated at the four-month study conclusion visit.

[figure not shown]

Inclusion criteria:

- Healthy, community-dwelling ambulatory post-menopausal women.
- Able and willing to sign informed consent.
- Ages: 55-65.
- Baseline serum 25OHD concentration > 10 ng/ml and < 60 ng/ml
- Not pregnant
- Willing to avoid use of cod-liver oil and non-study vitamin D supplementation; standard multiple vitamins containing ≤ 400 IU used no more than once daily will be allowed.
- Willing to utilize sunscreen of SPF-15 or higher when sun exposure for more than 15 minutes is expected.
- Willing to fast for 12 hours.

Exclusion criteria:

- Current hypercalcemia (serum calcium > 10.5 mg/dl) or untreated primary hyperparathyroidism.
- History of nephrolithiasis
- Baseline 24-hour urine calcium > 250 mg
- Known risk factors for hypercalcemia, e.g., malignancy, tuberculosis, sarcoidosis, Paget’s disease.
- History of any form of cancer within the past five years with the exception of adequately treated squamous cell or basal cell skin carcinoma.
- Known previous personal history of cardiovascular disease.
- Renal failure; defined as a calculated creatinine clearance (using the Cockroft-Gault approach) of ≤ 25 ml/minute.
- Severe end-organ disease, e.g., cardiovascular, hepatic, hematologic, pulmonary, etc., which might limit the ability to complete this study.
- Treatment with any drug known to interfere with vitamin D metabolism, e.g., phenytoin, phenobarbital.
- Known malabsorption syndromes, e.g., celiac disease, active inflammatory bowel disease, etc.
- Known allergy to chocolate.
- Use of medications known to alter bone turnover including bisphosphonates, estrogen, selective estrogen receptor modulators, parathyroid hormone, testosterone or calcitonin.
- Treatment with any active metabolites of vitamin D, e.g., calcitriol, within six months of screening.
- Use of tanning beds or salons or unwillingness to utilize sunscreen during periods of sun exposure of 15 minutes or longer.

All participants will be reimbursed $20 for each study visit. Project personnel will not receive recruiting incentives.

**STUDY VISIT EVENT FLOW CHART**

| **Time (months)** | **-1** | **0** | **1** | **2** | **4** |
| --- | --- | --- | --- | --- | --- |
| Study visit | Screen | Base | 1 | 2 | 3 |
| Consent | X |  |  |  |  |
| Medical history | X |  |  |  |  |
| Physical examination |  | X |  |  |  |
| Flow-Mediated Vasodilation |  | X |  |  | X |
| Radial Tonometry |  | X |  |  | X |
| Serum chemistry | X |  |  |  | X |
| Serum calcium |  | X | X | X |  |
| 24-hour urine calcium | X |  |  |  |  |
| 25(OH)D | X | X | X | X | X |
| PTH |  | X |  |  | X |
| Bone turnover markers |  | X |  |  | X |
| Fasting glucose |  | X |  |  | X |
| Fasting lipid panel |  | X |  |  | X |
| C-reactive protein (hsCRP) |  | X |  |  | X |
| Inflammatory Biomarkers |  | X |  |  | X |
| Dispense supplement |  | X | X | X |  |
| Assess compliance |  |  | X | X | X |
| Adverse event recording |  | X | X | X | X |

**Study Food Supplement:**

In this randomized trial, the study preparation will be a low calorie (~65 calories) cookie-like disc containing 2,500 IU of vitamin D3 or placebo produced by D-Rich Foods, Inc., Manitowoc, Wisconsin. Prior to study initiation the vitamin D content of the study preparation will be independently validated in the laboratory of Dr. [name] at the University of Wisconsin. Study participants will be asked to store the study supplement at room temperature. All unused study supplement will be returned and counted to document compliance.

**Study Randomization:**

An individual in the UW-Osteoporosis Research Center will be assigned to randomize subjects and package vitamin D/placebo “cookies” with labels. This individual will not participate in recruitment or data collection. We will ensure that the staff will remain blinded. The PRC has determined that this does not require their participation as this is not a drug.

**Laboratory Analyses:**

Serum chemistry, fasting glucose, fasting lipid panel, high sensitivity C-reactive protein (hsCRP), and urinary calcium determinations will be performed at General Medical Laboratories (Madison, WI) in routine clinical manner. Serum 25(OH)D concentration will be determined using reverse phase HPLC in the laboratory of [name] at the William S. Middleton VAMC (Madison, WI). Serum intact PTH and bone turnover markers will be run in [name] laboratory using commercially available kits. Plasma inflammatory biomarkers will be run at the Wisconsin Regional Primate Research Center Laboratory using commercially available assay kits.

**Safety:**

The risks of participation in this study are extremely low. Specific risks due to venipuncture include pain, bruising and infection.

Ultrasonography is used in FMD measurement. Arterial tonometry is used in pulse wave velocity, central aortic pressure and aortic augmentation index determination. These are low risk imaging procedures and are commonly used noninvasive techniques in the field of cardiovascular research to evaluate for endothelial dysfunction and arterial stiffness, which are considered surrogate markers for cardiovascular disease. No significant adverse outcomes have been reported from the use of these techniques.

Safety concerns regarding the potential development of D toxicity manifesting as hypercalcemia and/or hypercalcuria could potentially be raised. However, the risk of D toxicity with the doses utilized in this study is extremely remote. All high quality reports of D toxicity involve the long-term intake of > 40,000 IU daily. As the maximum vitamin D dose administered over the four months of this trial will be 300,000 IU, this study has a wide margin of safety. Based upon published literature and our clinical experience, we believe the risk of vitamin D toxicity from study supplementation to be negligible. Given this, we do not believe that a formal data and safety monitoring board is necessary.

Despite the wide safety margin noted above, we have taken additional steps to assure participant safety by use of study criteria selected to exclude those with existing hypercalcuria, conditions associated with increased likelihood of vitamin D toxicity, e.g., tuberculosis, and the rare individual with high vitamin D status. Adverse events will be collected and recorded on case report forms for completeness and reported at time of study publication.

An additional potential risk of study participation is breach of confidentiality. To minimize this risk, all data will be coded with subject’s initials and ID number. This is to ensure confidentiality. Moreover, all information collected in this research study will be stored on password-protected computers or in locked cabinets at the University of Wisconsin-Madison Osteoporosis Clinical Research Program.

**Data Handling and Analysis**

A study chart will be prepared for all participants and every study encounter will be recorded on case report forms (CRF’s). Hard copies of CRF’s and laboratory reports will be kept in each participant’s study chart, which will be stored in the study coordinator’s office at [name]. The study chart storage cabinet and the study coordinators office are both locked after working hours.

All study data will be entered into an Excel database by the study coordinator or designee. This database will reside on UW Osteoporosis Clinical Research server located at [name]. All OCRC computers are password protected and backed up daily utilizing a tape drive system. To assure that the data are transmitted reliably from paper into electronic form, two different individuals, or one individual on different days, will enter all data. Excel will verify that identical values were entered. Any discrepancies will be corrected by referring to the CRFs. At SMDC, all data will be entered into an access database. As at UW, dual-entry of data will be performed on 100% of data.

**ANALYTICAL APPROACHES AND CONSIDERATIONS**

1. **Power Calculation**

In experienced laboratories with excellent reproducibility (such as in [name] CV research lab), a 2% to 3% improvement in FMD can be detected in parallel-groups trials with about 25 to 45 subjects per treatment arm.(97-99) Power calculation shows that 37 subjects in each arm of this parallel group study should enable us to detect a 3% change in FMD with 80% power using a two-sample t-test with two-sided 5% level if the standard deviation of %FMD is similar to that observed by Sorenson.(98) Allowing for an 8% drop out rate, we plan to recruit 40 subjects per arm.

Endothelial function will be evaluated by measuring brachial artery FMD using ultrasound. Studies will be read in subject pairs (baseline and four months), blinded to study time point and treatment. Output data will include heart rate, brachial artery blood pressure, brachial artery diameter, reactive hyperemia VTI, and FMD at each time point.

Arterial stiffness will be determined from arterial tonometry using an AtCor Sphygmacor Px arterial tonometry system. Studies also will be read as described above. Output data will include heart rate, derived pulse wave velocity, central aortic systolic and diastolic pressure and aortic augmentation index, read independently and standardized to a heart rate of 75 bpm. The proposed sample size (37 per group or 74 total) will be sufficient to detect an ~10% reduction in pulse wave velocity with a standard deviation of approximately 15%, with at least 80% power using a two-sample, two-sided t-test with 5% level of significance. Thus, allowing for an 8% drop out rate, we plan to recruit 40 subjects per arm. Extrapolating from population-based studies,(100, 101) a 10% change in pulse wave velocity would predict a significant reduction in CVD risk.

1. **Statistical Analysis**

The primary endpoint is change in endothelial function from baseline after 16 weeks of vitamin D supplementation compared to placebo. The primary comparison will be made using a two-tailed Student's t-test. Multivariable linear regression modeling will be used to evaluate predictors of changes in FMD, including 25(OH)D levels, age, sex, and other CV risk factors. For the cross-sectional baseline analysis, Pearson correlations will be used to determine associations with FMD, and multivariable linear regression modeling will be used to determine independent baseline associations. Similar analyses will be performed for pulse wave velocity, central aortic pressure and aortic augmentation index.

Similar analyses will be performed for changes in plasma biomarker levels (hs-CRP, IL-6, TNF-, sICAM and sVCAM) from baseline to the 16-week follow-up. The proposed sample size of 37 subjects per group will permit us to detect differences between groups of 0.6-0.7 pg/ml in IL-6, 0.4-0.5 pg/ml in TNF- and 39-53 ng/ml in sICAM levels using a two-sample t-test with Type 1 error rate of 5% and 80% power if the standard deviations of cytokine levels are similar to those observed by Marketou.(102) As stated above, we plan to recruit 40 subjects per arm allowing for an 8% drop out rate.

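### The tests are on change from baseline, but the power statements cite SDs not stated to be of change; if they are SDs of a single level, 80% power needs a baseline to month 4 correlation of at least 0.5

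*Protocol*

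**What the plan says.** Under Statistical Analysis, the protocol defines the tested variable: "The primary endpoint is change in endothelial function from baseline after 16 weeks of vitamin D supplementation compared to placebo". The test is equally definite: "The primary comparison will be made using a two-tailed Student's t-test". No baseline covariate enters this comparison; regression is mentioned only for predictors of change.

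Under Power Calculation, 37 women per arm are said to be enough to "detect a 3% change in FMD with 80% power" by a two-sample, two-sided t-test at the 5% level, "if the standard deviation of %FMD is similar to that observed" in a cited study. The value is not printed, and the text does not say whether it is a between-woman SD of one measurement, a repeat-measurement SD or an SD of change. The same section sizes pulse wave velocity (PWV) separately, for a reduction of about 10% with an SD of about 15%, again without saying of what.

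For the biomarkers, the analyses are of changes to 16 weeks, but the detectable differences hold "if the standard deviations of cytokine levels are similar to those observed" in another cited study. The protocol gives no SD of change and no correlation between baseline and month 4 for any endpoint.

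**The concern.** A t-test on change is governed by the SD of change. The SD of a single measurement is a different quantity, and the two coincide only at one particular correlation between visits. A power figure that takes a level SD and applies it to a test on change therefore assumes that correlation without saying so.

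The biomarker paragraph does this in plain words. The FMD sentence does it on its plain reading, since it names the SD of %FMD and not of its change. If the true correlation is lower than the implied one, the trial has less power for 3 points than the protocol tells its readers. A null result could then be taken as stronger evidence against a 3-point effect than the design supports. If the correlation is higher, the trial is better powered than stated. Nothing printed lets a reader tell which.

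**Working it through.** **Inputs from the protocol.** 37 evaluable per arm; difference 3 (taken as percentage points of FMD); two-sided 5%; 80% power; test on change; no covariate. PWV: 10% and SD 15%. Biomarker detectable differences: IL-6 0.6–0.7 pg/ml, TNF 0.4–0.5 pg/ml, sICAM 39–53 ng/ml.

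**Assumptions, not in the protocol.** Equal variances at the two visits, and a baseline to month 4 correlation rho, varied from 0 to 0.8.

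**Step 1: the plan's own figures.** The exact (noncentral t, 72 df) standardised difference detectable with 80% power at 37 per arm is 0.660. PWV has 10/15 = 0.667, which gives 80.8% power, so that claim reproduces as stated. The FMD claim can only be solved backwards: SD = 3/0.660 = 4.54 points.

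**Step 2: from level to change.** SD(change) = SD(level) × √(2(1 − rho)). The factor is 1 exactly at rho = 0.5, larger below and smaller above.

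**Step 3: power for 3 points at 37 per arm, if 4.54 is a level SD.** The ANCOVA column uses a residual SD of 4.54 × √(1 − rho²).

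| rho | factor | SD of change | power, t-test on change | detectable at 80% | power, ANCOVA |
|---|---|---|---|---|---|
| 0 | 1.414 | 6.43 | 51% | 4.24 | 80% |
| 0.3 | 1.183 | 5.38 | 66% | 3.55 | 84% |
| 0.4 | 1.095 | 4.98 | 72.5% | 3.29 | 86% |
| 0.5 | 1.000 | 4.54 | 80% | 3.00 | 90% |
| 0.6 | 0.894 | 4.06 | 88% | 2.68 | 94% |
| 0.7 | 0.775 | 3.52 | 95% | 2.32 | 97.5% |
| 0.8 | 0.632 | 2.87 | 99% | 1.90 | above 99% |

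**Step 4: biomarkers.** Here the level SD is explicit. At rho 0.3 each detectable difference is multiplied by √1.4 = 1.18: IL-6 0.71–0.83 pg/ml, TNF 0.47–0.59 pg/ml, sICAM 46–63 ng/ml.

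**Step 5: PWV.** If the 15% is a level SD, power at rho 0.3 is 67%. If it is the SD of percentage change, the stated power stands. The text does not say which.

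**The case against.** The strongest reply is that, for FMD, the level reading is an inference. The protocol names no type of SD. The cited study is by its title about accuracy and reproducibility, and the paragraph opens by appealing to laboratories with excellent reproducibility. The SD may have come from repeat measurements or from change, in which case the threshold of 0.5 does not apply in this form. That stands, and it is why the point is conditional for FMD. It does not make the calculation checkable, and it does not touch the biomarkers, where the wording is explicit.

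It can also be said that nothing in the protocol points to a low correlation. Scans are read in pairs, blinded to time point and treatment, in a laboratory described as highly reproducible. That is fair: no value of rho can be defended from the protocol, so the table runs in both directions.

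Two further criticisms are tempting, and neither is supported:

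- A reader might infer that the preceding sentence, "a 2% to 3% improvement in FMD can be detected in parallel-groups trials with about 25 to 45 subjects per treatment arm", implies a smaller SD than 4.54. That needs 3% to be paired with 25 per arm and 2% with 45, and the sentence gives neither that pairing nor a power. At 80% power, 3% with 25 to 45 per arm implies SDs of 3.71 to 5.02, a range that contains 4.54.
- A reader might take FMD as the only justification of the trial's size. PWV is a separate one, and it reproduces.

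**Conclusion.** The power statements do not name the SD that the planned tests need. This is explicit for the biomarkers and is the plain, though unproven, reading for FMD. On the level-SD reading with equal variances, 80% power for 3 points requires rho of at least 0.5. Below that the shortfall is material (66% at 0.3, 51% at 0), and above it the trial exceeds its claim (95% at 0.7).

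A reader might conclude that the protocol used the wrong SD for FMD, or that 80 women are too few. The protocol supports neither: it prints no SD for FMD, so 37 per arm is unverifiable, not shown to be wrong. The issue merits correction because the protocol itself fixes the endpoint, the test and the SD cited, and because a better analysis is available from data already planned.

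**What to change.** Preferably, make the primary comparison an ANCOVA of month 4 FMD with baseline FMD as covariate, and do the same for PWV and the biomarkers. On the level-SD reading, 37 per arm then gives 80% power or more at any rho from 0 up, so the stated power no longer depends on an unstated correlation.

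If the t-test on change is kept, restate the claim for the variable tested: 37 per arm gives 80% power for 0.66 SD of the change, which is 3.0 points of FMD if the SD of change is about 4.5 or less. Print the SD used, its type and its source, and give the detectable difference over a range of SDs. Do the same for the biomarkers.

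In either case, state whether the 15% for PWV is an SD of level or of change.

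The cost is the rewriting of two paragraphs, plus one model term if ANCOVA is adopted. Baseline and month 4 measurements are already scheduled. The sample size stays at 80, with no added visits or procedures. If the t-test is kept, the printed detectable difference may become somewhat less favourable.

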**PROTOCOL OVERVIEW AND INTRODUCTION:**

In the United States, cardiovascular disease causes over one-third of all deaths and vitamin D deficiency is epidemic. An increasing body of data suggests that low vitamin D status adversely impacts the cardiovascular system. It is our fundamental hypothesis that vitamin D deficiency is a risk factor for cardiovascular disease by causing a cytokine mediated pro-inflammatory milieu leading to endothelial dysfunction. Moreover, we hypothesize that vitamin D supplementation will reduce inflammation, thus restoring endothelial function and thereby reducing cardiovascular disease risk. To begin testing these hypotheses, the specific aims of this pilot study are to investigate the effect of vitamin D baseline status (as defined by serum 25-hydroxyvitamin D [25(OH)D] measurement) and subsequent vitamin D therapy on endothelial function, arterial stiffness, and selected plasma biomarkers of inflammation.

This pilot research will be conducted in 80 post-menopausal women where 40 will receive vitamin D3 2,500 IU daily, the others matching placebo. This study will explore the effects of vitamin D on plasma markers of inflammation, endothelial function, and arterial stiffness. Postmenopausal women aged 55-65 years are chosen due to their highest risk for development of a subsequent new cardiovascular disease diagnosis. All study participants will have fasting laboratory and noninvasive vascular ultrasound studies performed at baseline and four months later. The primary outcome measure of this pilot study is change in markers of endothelial function and arterial stiffness with vitamin D3 therapy. Changes in plasma biomarkers of inflammation with vitamin D3 therapy are secondary outcome measures. If these hypotheses are correct, our long-term goals include investigation of the effect of vitamin D repletion on subclinical atherosclerosis and subsequent cardiovascular events.

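### The primary t-test on change in FMD is valid, but adjusting for the baseline FMD already scheduled in every woman would make it more efficient at almost no cost

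*Protocol*

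**What the plan says.** The Statistical Analysis section of the Protocol defines the endpoint: "The primary endpoint is change in endothelial function from baseline after 16 weeks of vitamin D supplementation compared to placebo". It then fixes the test: "The primary comparison will be made using a two-tailed" Student's t-test. No covariate is attached to that comparison.

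The same approach is carried to the other vascular measures ("Similar analyses will be performed for pulse wave velocity, central aortic pressure and aortic augmentation index") and, in the next paragraph, to the changes in the plasma biomarkers.

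Baseline values will exist. The overview states "All study participants will have fasting laboratory and noninvasive vascular ultrasound studies performed at baseline and four months later", and Specific Aim 2 adds that "brachial artery FMD and tonometry measurements will be repeated at the four-month study conclusion visit". The event flow chart marks FMD and tonometry at months 0 and 4. For FMD the Power Calculation section specifies "Studies will be read in subject pairs (baseline and four months), blinded to study time point and treatment".

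The only regression on change in FMD is described as "Multivariable linear regression modeling will be used to evaluate predictors of changes in FMD, including 25(OH)D levels, age, sex, and other CV risk factors". It is a search for predictors and is not the primary comparison. It lists neither randomised arm nor baseline FMD. The Study Randomization section describes no stratification.

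**The concern.** A raw change score subtracts the whole baseline value, which amounts to fixing the baseline slope at 1. Where the baseline to follow-up correlation is below 1, and the variance is the same at both visits, the best-fitting slope is rho. Subtracting the full baseline then adds avoidable noise. Change is also negatively correlated with baseline, so an arm that happens to start higher tends to show a smaller rise whatever the treatment does.

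At stake is precision on the primary endpoint of a trial with about 37 evaluable women per arm. The same loss applies to pulse wave velocity (PWV), central aortic pressure, augmentation index and the biomarkers. Validity is not at stake.

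**Working it through.** **Inputs from the Protocol (Power Calculation).** "37 subjects in each arm of this parallel group study should enable us to detect a 3% change in FMD", with 80% power, a two-sample t-test and a two-sided 5% level. The SD of FMD is given only by citation. The Protocol does not say whether it is the SD of one reading or of a change.

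**Assumptions.** Rho is not stated, so a range of 0.3 to 0.9 is shown. FMD variance is taken as equal at both visits.

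**Step 1: reproduce the plan's method.** The FMD figure cannot be checked directly because its SD is not printed. The PWV figure uses the same n and can be checked. With a 10% difference, SD 15% and 37 per arm, noncentral-t power is 80.8%, which agrees with the stated at least 80%.

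**Step 2: back-solve the FMD SD.** For 37 per arm, 3 points and 80% power by t-test on 72 df, the standardised effect must be 0.6602. The SD is therefore 3 / 0.6602 = 4.54 points (4.61 by the normal approximation).

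**Step 3: variance ratio.** With single-reading SD s:
- variance of change = 2s²(1 − rho)
- ANCOVA residual variance = s²(1 − rho²)
- ratio = (1 + rho)/2, which is 0.65, 0.75, 0.85 and 0.95 at rho 0.3, 0.5, 0.7 and 0.9

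**Step 4: charge ANCOVA for its cost.** It uses one more degree of freedom (71 instead of 72). Estimating the slope inflates the variance by 1 + 1/(2n − 4) = 1 + 1/70 = 1.014, or about 1.4%. Both are included below.

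**Step 5a: if 4.54 is the SD of change.** The t-test has 80.0% power at every rho by construction. The ANCOVA SD is 4.54 × √((1 + rho)/2) before the 1.4% inflation.

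| rho | t-test power | ANCOVA power, 37 per arm | ANCOVA n per arm for 80% |
|---|---|---|---|
| 0.3 | 80.0% | 93.2% | 25 |
| 0.5 | 80.0% | 89.5% | 29 |
| 0.7 | 80.0% | 85.5% | 33 |
| 0.9 | 80.0% | 81.4% | 36 |

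**Step 5b: if 4.54 is the SD of a single reading.** The SD of change is 4.54 × √(2(1 − rho)). The ANCOVA SD is 4.54 × √(1 − rho²) before inflation.

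| rho | t-test power | ANCOVA power |
|---|---|---|
| 0.3 | 65.8% | 83.0% |
| 0.5 | 80.0% | 89.5% |
| 0.7 | 95.1% | 97.3% |

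At rho 0.9 both are essentially 100%.

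**Step 6: where ANCOVA stops paying.** Setting (1 + rho)/2 × (1 + 1/70) = 1 gives rho = 2/1.0143 − 1 = 0.97. Above that the t-test is marginally better. At rho = 1 ANCOVA has 79.4% against 80.0% (reading 5a).

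**Step 7: conditional effect of imbalance (reading 5b).** The standard error of the baseline difference is 4.54 × √(2/37) = 1.06 points. An imbalance of one standard error shifts the expected change-score difference by (1 − rho) × 1.06, which is 0.74, 0.53 or 0.32 points at rho 0.3, 0.5 or 0.7. Against the 3-point target that is 25%, 18% or 11%. ANCOVA removes this shift.

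**The case against.** The strongest reply is that nothing here is an error. Endpoint, test and sample-size method agree with one another, and in a randomised, blinded trial a t-test on change is unbiased and keeps its type I error rate. The study also calls itself a pilot. All of this stands, and it limits the point to efficiency.

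Three stronger readings are tempting, and the Protocol does not support them.

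- **That baseline imbalance biases the result.** It shifts the estimate only conditionally on the allocation obtained. Over randomisation the shift averages to zero, and the t-test's standard error already includes that variation. Regression to the mean acts on both arms equally in expectation.
- **That the trial has only 66% power.** That figure needs both rho 0.3 and the assumption that the cited SD is of a single reading. The Protocol states neither. If the SD is of change, the t-test has 80% by construction.
- **That the gain must be large because FMD is noisy.** The Power Calculation section claims excellent reproducibility for its laboratory and specifies paired, blinded reading. If rho is near 0.9 the gain is about 1.4 points of power (81.4% against 80.0%).

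It may also be said that the planned regression on change in FMD has an open-ended list of predictors, so baseline FMD could enter it. It could, but that model is not the primary comparison and does not name treatment arm. An unseen analysis plan might add adjustment, but this Protocol does name its primary test, and names it without a covariate.

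**Conclusion.** The point holds as a nearly free improvement, not as a defect of validity. The Protocol fixes an unadjusted t-test on change although the baseline value of the same measure is scheduled for every woman. With equal variances at the two visits, ANCOVA needs (1 + rho)/2 of the change-score variance, less a charge of one degree of freedom and about 1.4%.

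The direction of the gain is secure for any rho below about 0.97. Its size is not, because neither rho nor the FMD SD is stated: it is material at rho 0.3 to 0.5 under either reading of the SD and small at 0.9.

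**What to change.** In the Statistical Analysis section, replace the sentence naming the primary test. The primary analysis becomes a linear model of month-4 FMD (or change in FMD) on randomised arm and baseline FMD, two-sided at 5%, reporting the adjusted difference between arms with its 95% confidence interval. Use the same model, each with its own baseline, for PWV, central aortic pressure, augmentation index and each biomarker. Keep the t-test on change as a sensitivity analysis. In the Power Calculation section, print the FMD SD used and say whether it refers to a single reading or to change.

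The cost is a few sentences of text, one degree of freedom and about 1.4% in variance. No visit, scan or assay is added and the sample size need not change. The edit should be made before unblinding, so that the choice between the two analyses cannot depend on the results.
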